## 5.2 Use of co-intervention

Use of contraception pre-surgery:

- If patients already use some form of hormonal contraception: continuation of the treatment.
- If patients have natural cycle: start hormonal contraception during next menstruation for at least 4 weeks preoperatively

Duration of use of the hormonal treatment will be registered.

Types of allowed contraception:

- Combined oral contraception (classic pil)
- Vaginal ring (eg Nuvaring, Izzyring,...)
- Progesteron only pil

- Hormone releasing intrauterine device (for example: Mirena, Kyleena,...) are allowed provided that they are combined with oral/vaginal contraception for adequate ovarioistasis

The use of GnRH analogues (both preoperatively and in the first 3 months postoperatively) is not allowed.

Other chronic use of medication can be continued but should be registered (for example: analgesics...).

## 6. METHODS

### 6.1 Study parameters/endpoints

#### 6.1.1 Main study parameter/endpoint

Evaluation of serum AMH before (baseline) and after (at 3 months follow up) laparoscopic treatment of endometrioma(s):

#### 6.1.2 Secondary study parameters/endpoints

- AMH difference/cyst surface between baseline and at 3, 6 and 12 months post-operative with a correction for the cyst surface (since the volume of the cyst may be responsible for more/less influence on the ovarian reserve)
- AMH modifications at 6 and 12 months follow up
- Cyst recurrence rate at 3, 6, 12 and 24 months postoperatively (visualized by transvaginal ultrasound)
- Clinical pregnancy (as defined by the ICMART (16) as a pregnancy diagnosed by ultrasonographic visualization of one or more gestational sacs or definitive clinical signs of pregnancy. It includes ectopic pregnancy. Note: Multiple gestational sacs are counted as one clinical pregnancy.)
- Ectopic pregnancy (as defined by the ICMART (16) as a pregnancy in which implantation takes place outside the uterine cavity)
- Miscarriage (defined as a spontaneous loss of pregnancy)
- Live birth (as defined by the ICMART (16) as the complete expulsion or extraction from its mother of a product of fertilization, irrespective of the duration of the pregnancy, which, after such separation, breathes or shows any other evidence of life, such as heart beat, umbilical cord pulsation, or definite movement of voluntary muscles, irrespective of whether the umbilical cord has been cut or the placenta is attached.

- Evolution of pain patterns pre- and postoperatively: each endometriosis related pain complaint will be evaluated using the NRS scale at each visit.
- POI postoperatively

### 6.1.3 Other study parameters

#### Baseline data:

- age of the participant
- use of contraception + type
- smoking
- previous surgery for ovarian cysts
  - laparoscopy
  - laparotomy
- previous surgery for endometriosis
  - number of surgeries
- indication for surgery:
  - pain
  - Infertility
- pain pattern (+NRS for each parameter)
  - dysmenorrhea
  - chronic pelvic pain/non menstrual pelvic pain
  - dyspareunia
  - dyschezia
  - dysuria
- infertility:
  - duration of infertility
  - primary or secondary infertility
- gravida/para
- BMI (kg/m^2)
- Number of endometriomas
- Diameter of all the cysts (measured in 3 orthogonal planes in mm)
  - Cyst 1
  - Cyst 2
  - ...
- Cyst wall surface
- Uni or bilateral endometriomas
- Baseline AMH value

Surgical data:

- Total Operative time (min)
- Operative time for endometrioma (min)
- Hemostatic method used to manage the bleeding on each ovary
  - Not required (no bleeding)
  - Selective bipolar coagulation + hemostatic device used + power settings
  - Suturing
  - Hemostatic sealants
- rASRM points and stage
- EFI
- Hospital stay (days)
- Follow up (months)
- Complications until 3 months postoperatively as defined by the Clavien-Dindo classification (21)

Postoperative follow-up:

- Baseline questionnaire concerning pain pattern (+NRS for each parameter) at 3, 6, 12 and 24 months follow up
  - dysmenorrhea
  - chronic pelvic pain/non menstrual pelvic pain
  - dyspareunia
  - dyschezia
  - dysuria
- Child wish, if present report management in past period (at 3, 6, 12 and 24 months follow up):
  - Non-ART management:
    - Spontaneously +/- ovulation induction
    - IUI
  - ART management:
    - IVF
    - ICSI
    - Egg donation
- Transvaginal ultrasound (at 3, 6, 12 and 24 months follow up)
- AMH value at 3\*, 6 and 12 postoperatively (\*standard care)

## **6.2 Randomization, blinding and treatment allocation**

Patients fitting the inclusion criteria and consenting to participate are randomly assigned according to a computer-generated randomization list using the method of block randomization (using varying block sizes) to allocate them in proportion, at 1:1, either to Group 1 (combined technique) or Group 2 (CO2 laser vaporization).

Randomization will be done maximally 2 months before the intervention and minimally 1 hour before start of the intervention by the (sub)investigator of each center. Block randomization per study center will be used to ensure allocation of equal numbers of subjects in each group per center.

Blinding of the surgeon is not possible. Blinding of surgeons/patients during postoperative follow up is not feasible and is assumed to not influence the primary outcome. Indeed, bias due to lack of blinding is expected to be negligible since the primary outcome measured is clear and unambiguous (measurement of AMH).

## **6.3 Study procedures**

### **6.3.1 Participants flow**

## STUDY FLOW CHART

[figure not shown]

### 6.3.2 Time requirements

Patient recruitment will start after approval by the ethics committee. Estimated inclusion time of 60 months (initially estimated inclusion time of 24 months, due to the COVID-19 pandemic important delay in recruitment for which extension of inclusion time with another 36 months).

Primary outcome will be analyzed at 3 months follow-up postoperatively. Secondary outcomes will be analyzed at 24 months follow-up postoperatively. If necessary, extend with 9 months to allow full follow-up of pregnancies until delivery.

### 6.3.3 Trial monitoring and patient visits

All patients will be seen by the principal/subinvestigators or by one of his/her staff members at the following moment:

- Screening = standard of care  
     Consultation for discussion of the standard preoperative examination, study information will be given if patient is eligible for inclusion.  
     AMH value = standard of care for patients planned for laparoscopic surgery for an endometriotic cyst (part of the screening process)
- Baseline = study visit (can be combined with screening)  
     Completion of the informed consent forms
- Elective hospitalization for surgery = standard of care  
     Randomization  
     AMH value = study sample
- 3 months postoperatively (visit window: minimally 3 months postoperatively + 2 weeks)  
     Visit with postoperative checkup, complications assessment using the Clavien-Dindo classification, anamnesis concerning pain and child wish and transvaginal ultrasound = standard of care  
     AMH value = standard of care
- 6 months postoperatively (+/- 2 weeks)  
     Visit with anamnesis concerning pain and child wish and transvaginal ultrasound = standard of care  
     AMH value = study sample
- 12 months postoperatively (+/- 2 weeks)  
     Visit with anamnesis concerning pain and child wish and transvaginal ultrasound = standard of care

AMH value = study sample

- 24 months postoperatively (+/- 2 weeks)

Visit with anamnesis concerning pain and child wish and transvaginal ultrasound = standard of care

| Procedures                                | Visits    |           |                 |           |          |           |           |
|-------------------------------------------|-----------|-----------|-----------------|-----------|----------|-----------|-----------|
|                                           | Screening | Baseline* | Hospitalization | Follow up |          |           |           |
|                                           |           |           |                 | 3 months  | 6 months | 12 months | 24 months |
| History/clinical exam                     | x         |           |                 |           |          |           |           |
| Informed consent                          |           | x         |                 |           |          |           |           |
| Eligibility assessment                    |           | x         |                 |           |          |           |           |
| Randomization                             |           | x         |                 |           |          |           |           |
| Laparoscopic surgery (group 1 vs group 2) |           |           | x               |           |          |           |           |
| Postoperative check-up                    |           |           |                 | x         |          |           |           |
| Complication assessment                   |           |           |                 | x         |          |           |           |
| Anamnesis                                 |           |           |                 | x         | x        | x         | x         |
| Ultrasound                                |           |           |                 | x         | x        | x         | x         |
| AMH-value                                 | x         |           | D-1*            | x         | x*       | x*        |           |

\* = study sample/visit

Blood samples for AMH measurements (using Roche ECLIA AMH kit): standard of care sample will be done at the laboratory of each participating center – study samples will be sent to the laboratory of UZ Leuven.

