## 2. OBJECTIVES

Primary Objective: To assess the effect of conservative laparoscopic treatment of endometrioma(s) on ovarian reserve as reflected by AMH in patients planned for laparoscopic CO2 laser surgery. For the primary outcome evaluation of serum AMH will be done before (baseline) and after (at 3 months follow up) laparoscopic treatment of endometrioma(s).

The primary study hypothesis is that CO2 laser vaporization only of the cyst wall will result in less ovarian damage than when the combined technique is performed. The null hypothesis is that CO2 laser vaporization of the cyst wall does not result in better preservation of the ovarian reserve.

AMH was chosen as marker of the ovarian reserve since it is the only marker being menstrual cycle independent and easily measured. AMH measurements will be analyzed using the Roche ECLIA AMH kit (available in all centers). Multiple determinants (as

described above) influence AMH values, ideally AMH measurement is done in a natural regular cycle of non-smoking and non-pregnant women. In the daily clinical practice this is not always the case due to the variations in patients' clinical presentations.

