### 6.3.4 Study costs

Blood samples for AMH measurements: total blood samples: 5

Kit used for AMH measurement: Roche ECLIA AMH: cost per analysis: 27€

(2 paid by the patients – 3 for the study =  $3 \times 27\text{€} = 81\text{€}$ )

Total cost for AMH measurement based on a sample size of 92 patients =  $92 \times 3 \times 27\text{€} = 7452\text{€}$

Consultations and transvaginal ultrasounds = standard of care.

Organization of the study is done by a trainee in gynecology and obstetrics/PhD student (cost of a PhD student/year: for the full project duration: first year 41343,40€– second year 43140,99€– third year 45179,77€– fourth year 47071,49€). Estimated time requirement per week for this study: 1 day/week.

Help of a study nurse (cost of a study nurse/year: 45000€). Estimated time requirement per week for this study: 0,5 day/week.

Statistical analysis will be done by a statistician ([name]).

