### **8.3 Primary study parameter(s)**

Evaluation of serum AMH at 3 months follow up.

It concerns an intention to treat analysis. All participants will be included in the analysis in the groups to which they were originally assigned, regardless of what subsequently occurred.

To handle the presence of missing values (due to dropout or to pregnancy, in the latter case AMH values after pregnancy are put on missing), a constrained longitudinal data analysis (cLDA, cfr Liang and Zeger, 2010) will be used instead of an ANCOVA to evaluate the differences between the groups in the final analysis. In this approach both the baseline and post-baseline values are modeled as dependent variables, as opposed to a longitudinal ANCOVA model in which the baseline value is included as a covariate. Although the baseline measure is included in the response vector in cLDA, the true baseline means are constrained to be the same for different treatment groups due to randomization, and this analysis provides an adjustment for the observed baseline difference in estimating the treatment effects. Center will be added as a factor in the model. A (logarithmic) transformation of the AMH will be considered to obtain a more symmetric distribution of the model residuals. Using a direct likelihood approach for the cLDA model, a subject with a missing measurement at three months is not excluded from the analysis. As such, the analysis does not assume missing completely at random (MCAR), but is still valid under missing at random (MAR).

References: Liang, K. Y. and Zeger, S. (2000). Longitudinal data analysis of continuous and discrete responses for pre-post designs. *Sankhya: The Indian Journal of Statistics, Series B* 62, 134–148.

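### The 3-month AMH is assayed locally and the D-1, 6- and 12-month AMH centrally, so any laboratory offset is confounded with the primary visit, and a centre main effect cannot remove it

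*Protocol*

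**What the plan says.** The primary objective (Protocol, Section 2) involves two time points: "For the primary outcome evaluation of serum AMH will be done before (baseline) and after (at 3 months follow up"). Section 8.3 names the primary parameter as "Evaluation of serum AMH at 3 months follow up".

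Section 6.3.3 gives the 3-month sample the label "AMH value = standard of care". The visit table agrees: the study-sample asterisk is on D-1, 6 and 12 months, but not on screening or 3 months. The note under the table sets the laboratory by that label: "standard of care sample will be done at the laboratory of each participating center – study samples will be sent" to UZ Leuven. The budget in Section 6.3.4 has the same split of the five samples: "2 paid by the patients – 3 for the study".

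For the primary analysis, Section 8.3 puts baseline and post-baseline AMH together in the response vector of a constrained longitudinal data analysis (cLDA) and says "Center will be added as a factor in the model". Section 8.4 extends this model to 6 and 12 months. The protocol mentions no laboratory term, cross-calibration or central re-assay of the 3-month sample.

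**The concern.** The sample that carries the primary endpoint is the only postoperative AMH not measured in the central laboratory. At Liège, Antwerp and Brussels the laboratory changes between D-1 and 3 months, and changes back between 3 and 6 months. A systematic difference between a local laboratory and UZ Leuven cannot then be told apart from a change in AMH over those intervals.

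This matters for what the trial sets out to describe. Section 1 asks whether, and how much, each procedure affects ovarian reserve, judged from changes in AMH, and it cites evidence of recovery within months of surgery. A local laboratory that reads low would look like a surgical loss at 3 months followed by recovery at 6. One that reads high would hide a loss. The AMH-to-cyst-surface ratio in Section 8.4 is analysed in the same way and has the same problem.

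**Working it through.** **1. Laboratory by visit (Section 6.3.3)**

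| AMH sample | Status | Laboratory |
|---|---|---|
| Screening | standard of care | own centre |
| D-1 | study | UZ Leuven |
| 3 months | standard of care | own centre |
| 6 months | study | UZ Leuven |
| 12 months | study | UZ Leuven |

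Two standard-of-care and three study samples make five, as in Section 6.3.4. For Leuven patients the local laboratory appears to be the central one, so three of the four centres switch.

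**2. The plan's own figures.** Section 8.1: 30% of 1.9 is 0.57 ng/mL. With SD 0.9 and two-sided alpha 0.05, the t-test needs 41 per arm (power 80.9%; 40 per arm gives 79.9%), so 82 in total, and 82/0.9 rounds up to 92. Section 6.3.4: 92 × 3 × 27 = 7,452 euro. All reproduce, and this point changes none of them.

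**3. What the model can absorb.** Write the mean at centre c and visit t as a visit effect, plus a centre effect, plus the treatment effect after surgery, plus an offset d(c) wherever the sample was assayed locally, with d = 0 for Leuven.
- *D-1 as baseline:* d(c) is present at 3 months only. The centre effect is one constant over all visits and cannot represent it. The average of d(c) goes into the 3-month visit effect; the spread between centres goes largely into the residual.
- *Screening as baseline:* d(c) is present at both visits of the primary model. A constant offset is absorbed by the centre effect. The mismatch enters when the 6- and 12-month values are added.

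**4. Size for the change over time (D-1 as baseline).** With an assumed -10% at three of four equal centres, the average is (0 - 10 - 10 - 10)/4 = -7.5%, which reads as about a 7.5% loss.

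A simulation of the two-visit model (80 patients, four equal centres, 1:1 within centre) shows the same mechanism on the ng/mL scale. The laser arm had a 3-month mean of 1.9 and an assumed true change of -0.60. With +10% at three centres the expected distortion is 0.75 × 0.10 × 1.9 = 0.14; the estimate was -0.46 instead of -0.60. With +20% it was -0.32.

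**5. Between-arm contrast.** With no true effect, the estimate averaged 0.00 with either centre specification. With a true -0.57 on the untransformed scale it was only rescaled: at +10% in three centres, -0.57 × 1.075 = -0.61, and the simulations gave -0.60 to -0.61. Power was about 88% or more in every case run (assumed correlations 0.5 to 0.85).

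**6. Precision.** Log-scale SD = sqrt(ln(1 + (0.9/1.9)²)) = 0.450. With an assumed baseline correlation of 0.7, the conditional variance is 0.450² × (1 - 0.7²) = 0.1032. The two-visit model was simulated with a zero offset at Leuven and random offsets at the other three centres:

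| Assumed SD of offsets | Model SE too large by about |
|---|---|
| 10% | 2% |
| 15% | 4% |
| 20% | 7% |

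A harsher case, with fixed offsets of 0, +20%, -20% and +20% and correlation 0.85 under the null, gave a model SE of 0.134 against an empirical SE of 0.117, and a type I error of 2.6%. Centre-by-time terms brought this to 0.115 against 0.116, and 5.0%.

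**The case against.** - **The primary hypothesis is comparative.** Section 6.2 blocks randomisation by centre, so both arms carry the same offsets. This stands. The comparison is unbiased under the null, and any miscalibration is slightly conservative.
- **One kit is used everywhere.** Sections 2 and 6.3.3 specify the Roche ECLIA assay for all centres. This stands as mitigation. It makes a large offset less likely but does not rule one out, and no cross-check is planned.
- **The baseline may be the screening sample.** Section 8.2 says that randomisation follows baseline measurement. Section 6.2 allows randomisation up to two months before surgery. The visit list in Section 6.3.3 places it at hospitalisation, and the table places it at the baseline visit. With a screening baseline, the two-visit primary model is protected against a constant offset. This stands, so the effect on the primary model is conditional. The mismatch in the 6- and 12-month extension holds on either reading. Screening has its own weakness: under Section 5.2, women with a natural cycle start contraception before surgery, and Section 1 says that contraceptive use lowers AMH. Women already on contraception continue it, so this concerns only some patients.
- **Centre as a factor may include centre-by-time terms.** The exact terms could be given in an analysis plan that is not shown. That would settle the SE, but an analysis plan cannot change where the protocol has the 3-month sample assayed.

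**Conclusion.** The laboratory split by visit is certain from the text, and a centre main effect cannot represent an offset that depends on visit. The damage is to the within-arm change and the 3-, 6- and 12-month course, with a small loss of precision: about 7.5% of apparent loss for a -10% offset at three of four equal centres, and an SE about 2% to 7% too large for offset SDs of 10% to 20%. These sizes rest on assumptions that are not in the documents: the offsets themselves, equal centre sizes, a baseline correlation of 0.7 and D-1 as baseline.

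A reader might infer three stronger things that the documents do not support:
- *The treatment comparison is biased.* It is not under the null, because of blocking by centre.
- *The SE is 5%, 10% or 18% too large.* Adding the whole offset variance to the residual, sqrt((0.1032 + b²)/0.1032) for b = 0.10, 0.15 and 0.20, gives 1.047, 1.104 and 1.178. This ignores that Leuven has no offset and that the visit and centre effects take up part of the rest.
- *A 10% offset uses up a third of the 30% target.* The 30% is a difference between arms, whereas an offset common to both arms cancels in that difference.

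**What to change.** 1. **Name the baseline sample** (screening or D-1) in Sections 6.1.1 and 8.3, and reconcile the statements on when randomisation takes place. If D-1 is chosen, Section 8.2 must allow for a baseline drawn after randomisation. No cash cost.
2. **Use centre-by-time terms instead of a centre main effect** in the cLDA. This adds (4 - 1) × (2 - 1) = 3 degrees of freedom in the two-visit model and (4 - 1) × (4 - 1) = 9 when 6 and 12 months are included. It restores SE calibration. It does not recover the true change over time at the three centres that switch laboratory.
3. **To recover that change**, for patients still to reach 3 months, send an aliquot of the existing 3-month draw to UZ Leuven, use that value in the analysis, and keep the local result for care. The assay cost is at most 92 × 27 = 2,484 euro, plus shipping and handling. The grant leaves 14,065 - 7,452 = 6,613 euro after the planned assays, and that also has to cover statistical support and the eCRF (Section 6.3.5).
4. **For 3-month samples already assayed locally only**, report the within-arm change and the 3-to-12-month course with the laboratory switch stated as a limitation.

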### 6.3.4 Study costs

Blood samples for AMH measurements: total blood samples: 5

Kit used for AMH measurement: Roche ECLIA AMH: cost per analysis: 27€

(2 paid by the patients – 3 for the study =  $3 \times 27\text{€} = 81\text{€}$ )

Total cost for AMH measurement based on a sample size of 92 patients =  $92 \times 3 \times 27\text{€} = 7452\text{€}$

Consultations and transvaginal ultrasounds = standard of care.

Organization of the study is done by a trainee in gynecology and obstetrics/PhD student (cost of a PhD student/year: for the full project duration: first year 41343,40€– second year 43140,99€– third year 45179,77€– fourth year 47071,49€). Estimated time requirement per week for this study: 1 day/week.

Help of a study nurse (cost of a study nurse/year: 45000€). Estimated time requirement per week for this study: 0,5 day/week.

Statistical analysis will be done by a statistician ([name]).

### **6.3.5 Budget and funding**

14065€ has been granted by the Fond Academische Studies of the University Hospitals Leuven. Budget for consumables (study related AMH measurements), statistical support and use of the eCRF (Redcap) for the duration of the study.

